### Process: combined arm

The first program of the Combined arm will be *Toddlers Without Tears,* the series of three parenting group sessions running for approximately 2 hours each, offered to all families randomised to this arm. An MCH nurse and psychologist with experience in facilitating parenting groups will deliver each session to groups of 4–12 parents. The sessions involve role plays with practice activities, multi-choice scenario discussions, parent education activities utilising parent hand outs, and summarising ideas to practice at home directly with toddlers. All sessions are supported by *Toddler without Tears* parent handouts. Parents who do not attend a session are mailed the relevant parent handouts and offered a 30 minute telephone consultation with a psychologist to discuss the key messages provided in the group session and handouts.

Families in this Combined arm group that are identified with a child ‘at risk’ at age two years will be offered the *Family Check-Up.* We estimate that ≈ 10% of families will be eligible for the *Family Check-Up*; these families will receive a phone call from the research team inviting them to participate in the *Family Check-Up* program. Families will be free to accept or decline this offer.

### Process: targeted arm

Families in the Targeted arm will be offered the *Family Check-Up* program if their child is found to be ‘at risk’ at 2 years of age, as per the process detailed above. Eligibility criteria and intervention will proceed in the same way as for the Combined arm. It is anticipated that *Family Check-Up* uptake in this Targeted arm will be lower than in the Combined arm, as all families in the Combined arm will have been offered some help through the *Toddlers Without Tears* program and may find the recruitment approach into the *Family Check-Up* a more natural extension of assistance.

### Process: usual care arm

Families in the Usual care arm will receive only usual care from their MCH nurse and other health and social services in their community. This does not include the *Toddlers Without Tears* or *Family Check-Up* program.

### Outcome measures

Outcomes will be multi-source, collected from both primary and secondary carers. All families complete an intake questionnaire at child age 8 months and a baseline questionnaire at child age 12 months, and will be asked to complete one postal questionnaire annually around the child’s birthday until child age five years. The 8-month questionnaire measures child demographic characteristics (age, gender), family characteristics (marital status, parent age, education level, country of birth, main language spoken at home) as well as potential confounders including: (1) psychosocial risk factors measured by the Family Psychosocial Screening Instrument (12 items, public health screen for domestic violence, parent substance abuse, social isolation) [34]; (2) conflicts over child-rearing measured by the Parenting Problem Checklist (17 items) [35]; (3) relationship dissatisfaction measured by the Partner Relationship Scale (7 items) [36]; and infant temperament measured by the Maternal Child Difficulty Rating (1 item) [37]. Baseline questionnaire measures are described in Table 1.

**Table 1 T1:** Secondary outcome measures and time-points

**Construct**	**Measure**	**Administration time points (child age in yrs)**					**Rationale for use**
		**Baseline***	**2y**	**3y**	**4y**	**5y**	
**Parent questionnaire measures:** Primary carer ■ Secondary carer ▴							
Child major health or developmental diagnoses	Parents’ Evaluation of Developmental Status (PEDs) [38]	■					Children with major diagnoses are excluded.
Child quality of life	PedsQL 4.0 Generic Core Scale [39]			■	■	■	Child health-related quality of life.
Parenting practices	Over involved/protective parenting scale [12]	■	■	■ ▴	■ ▴	■▴	Assessment of parenting practices.
Parent mental health	Depression Anxiety Stress Scales (DASS21) [40]	■	■	■▴	■ ▴	■▴	Impact on parental mental health.
Parent quality of life	Assessment of Quality of Life 6D [41]	■	■	■	■	■	Independent living, mental health, coping, relationships, pain and senses.
Costs	Child and adult health service use		■	■▴	■ ▴	■▴	Intervention process evaluation (policy/decision makers considering translation/dissemination).
Feedback: *Family Check-Up*	Parents acceptability and usefulness rating of the intervention			■			Intervention process evaluation (translation/dissemination uptake by families).
Feedback: *Toddlers Without Tears*	Parents acceptability and usefulness rating of the intervention		■	■			Intervention process evaluation (translation/dissemination uptake by families).
**Health professional measures: MCH nurses▴**							
Construct	Measure	Administration time points (child aged yrs)					Additional information
		15 & 18 months	2	3	4	5	
Delivery/Fidelity *Toddlers Without Tears* Program	Group sessions content checklists	**▴**	**▴**				Integrity of intervention delivery. Adapted for this study.

* Baseline includes the 8 and 12 month questionnaires.

We have two primary outcome measures: the Child Behavior Checklist (CBCL/1.5-5 years) – a widely used and validated 99-item measure of externalising and internalising behaviours [32] and the nurturing and harsh discipline subscales of the Parenting Behavior Checklist [14]. All primary outcomes will be measured at 4 time points. All secondary measures and process evaluation measures are reported in Table 1.

### Prognostic factors

We will adjust analyses for potential prognostic factors measured in the 8-month questionnaire.

### Economic evaluation

Costs of delivering the *Toddlers Without Tears* and *Family Check-Up* programs (e.g. materials and training) will be measured largely through research team and MCH records. Costs of families’ use of health and other services outside of the study (e.g. other psychologists, psychiatrists, media resources) will be measured by parental report. Measured resource use will be valued using existing unit cost estimates (e.g. Medicare fee schedule rates). Economic evaluation will be presented first as a cost-consequences analysis [42], which allows policy makers to compare the incremental costs with all outcomes of interest – i.e. child behaviour, parenting, caregiver mental health and impact on health-related quality of life. Economic evaluation will then present a cost-utility analysis, comparing incremental costs to incremental parental quality of life (as measured by AQoL-6D) [41].

### Power calculation and study population

The sample size is based on detecting a reduction of 0.25 of a standard deviation (SD) in the mean scores for externalising behaviour problems on the CBCL at age 5 years with 80% power and 2-sided significance level of 0.05. Ignoring clustering effects, 252 children would be required in each of the three trial arms (756 in total). As nine LGAs are included in the study, we anticipated from our previous trial [26] that 60 MCH clusters would be recruited with 20 of these allocated to each trial arm. For an individually randomised trial 12.6 (756/60) children would need to be recruited from each MCH centre. In order to allow for correlation between the responses of children from the same cluster [43], we need to inflate this figure using a formula provided by Campbell [44] that is appropriate when the number of clusters is fixed and known in advance, but the number of participants required per cluster needs to be calculated. Using this formula and assuming an intra-cluster (intra-MCH centre) correlation coefficient of 0.03 (estimated from our previous trial) for the CBCL externalising behaviour problems outcome, 393 subjects are required in each trial arm [27]. Allowing for 20% attrition by age five, we need to recruit 492 children in each trial arm (1476 in total).

### Analyses

We will compare mean SIEFA scores and child gender for those eligible families who chose to participate vs those who chose not to participate. We will also describe the reasons they chose not to take part including ‘too busy’, ‘not interested’, and ‘moving house’. Demographic and baseline characteristics at the MCH cluster and family levels will be summarised using means and standard deviations (or medians and inter-quartile ranges) for quantitative characteristics and percentages for categorical characteristics. Analyses will use the ‘intention to treat’ principle, with families that provide outcome data analysed according to the trial arm to which their MCH centre was randomised. All analyses will allow for correlation between outcome scores of participating families from the same MCH cluster. Primary analyses will compare the mean CBCL externalising and internalising scores reported by the primary caregiver at ages 3, 4 and 5 years across the three trial arms.

Secondary analyses will compare the CBCL scores reported by the secondary caregiver and, for both caregivers, compare mean parenting subscale scores (nurturing, harsh discipline, inappropriate expectations, over-involved/protective), mean parental depression, anxiety and stress scores, and mean parent quality of life scores across the trial arms. Mean health care costs reported by the primary caregiver will also be compared between trial arms. Tests of interaction will be used to investigate whether the intervention effects differ between outcomes reported by the primary and secondary caregivers. If there is evidence at the 5% level of significance of differential effects then separate effect sizes will be reported for each caregiver, otherwise a single overall effect size will be reported.

Analyses of quantitative outcomes (unadjusted and adjusted for potential prognostic factors measured at baseline) will be implemented using random effects linear regression fitted using restricted maximum likelihood estimation [45]. Intra-cluster (intra-MCH centre) correlation coefficients will be reported for the study outcomes to aid the planning of future cluster randomised trials in this area. The take up of the *Family Check Up* program (binary outcome) amongst ‘at risk’ families will be compared between the Combined and Targeted arms by marginal logistic regression models using Generalised Estimating Equations with information sandwich estimates of standard error and assuming an exchangeable correlation structure [46].

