The *Families in Mind* trial therefore aims to compare the effectiveness, cost-effectiveness and population reach and uptake of a targeted approach alone (the *Family Check-Up* program) with a combined universal (the *Toddlers Without Tears* group parenting sessions) and targeted approach in the Australian population. Both programs will be delivered through existing child health workforces in the state of Victoria, and will be compared to the provision of usual care alone (‘control’ group).

We hypothesise that families offered this targeted program, either alone or in combination with this universal program, will have better outcomes than families who are not offered these programs. Outcomes include mean scores at child age three, four and five years for:

a) child externalising and internalising behaviour problem s (primary outcome)

b) harsh discipline and nuturing parenting practices (primary outcome), and

c) parental mental health (secondary outcome)

Additionally, we hypothesise that uptake of the targeted program by ‘at risk’ families will be greater with the combined approach where the universal parenting program precedes the targeted program (to reduce stigma), than with the targeted program alone.

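### Nurturing and harsh discipline are primary outcomes in two places and secondary in the analysis section, and the powered test is one of several primary comparisons with none named as deciding

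*Protocol article*

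**What the plan says.** All references are to the protocol article.

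- **Hypotheses (end of the Background).** The outcomes are introduced with "Outcomes include mean scores at child age three, four and five years for", and the second item reads "b) harsh discipline and nuturing parenting practices (primary outcome), and". Child externalising and internalising problems are also marked primary; parental mental health is marked secondary.
- **Outcome measures, text after Table 1.** "We have two primary outcome measures: the Child Behavior Checklist (CBCL/1.5-5 years" opens the statement, and the second measure is given as "and the nurturing and harsh discipline subscales of the Parenting Behavior Checklist". It adds: "All primary outcomes will be measured at 4 time points".
- **Analyses, primary.** "Primary analyses will compare the mean CBCL externalising and internalising scores reported by the primary caregiver at ages 3, 4 and 5 years". This comparison takes in all three arms.
- **Analyses, secondary.** Alongside secondary-carer CBCL scores, parental mental health, and parent quality of life, the secondary analyses will, "for both caregivers, compare mean parenting subscale scores (nurturing, harsh discipline, inappropriate expectations, over-involved/protective".
- **Power calculation and study population.** The trial is sized to detect a 0.25 SD reduction in externalising problems "on the CBCL at age 5 years with 80% power and 2-sided significance level of 0.05".

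**The concern.** The three statements about the parenting subscales cannot all hold. If the results showed an effect on nurturing or harsh discipline but none on child behaviour, the trial would be positive on a primary outcome under the hypotheses and the Outcome measures section, and negative under the Analyses section. The authors could cite the article for either reading after seeing the data. The Background gives some reason to take that pattern seriously: the earlier trial of the universal program reported modest gains in parenting and no prevention of behavioural or emotional problems.

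The second difficulty is the link between power and analysis. The power statement concerns one score at one age. The primary analysis covers two scores, three ages and three arms, and nothing identifies the powered comparison as the one that decides the trial. The reader cannot tell to which test the 80% belongs.

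**Working it through.** **1. Status of the parenting subscales, side by side**

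| Place | Nurturing and harsh discipline |
|---|---|
| Hypotheses (Background) | primary |
| Outcome measures | primary (second of two measures) |
| Analyses | no primary analysis; listed under secondary analyses |

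Separating primary outcomes from primary analyses does not reconcile these entries. The Analyses section gives the two subscales no primary analysis, and groups them with outcomes that the hypotheses or Table 1 call secondary.

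**2. The stated sample size reproduces**

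Inputs from the power section: difference 0.25 SD, two-sided alpha 0.05, power 80%, 20 clusters per arm, ICC 0.03, attrition 20%.

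- Without clustering: n = 2 × ((1.960 + 0.842)/0.25)² = 251.2, so 252 per arm (stated: 252).
- Fixed number of clusters: m = n(1 − ICC)/(k − n·ICC) = 252 × 0.97/(20 − 7.56) = 19.65 per cluster; × 20 = 393 per arm (stated: 393).
- Attrition: 393/0.80 = 491.25, so 492 per arm and 1476 in total (as stated).

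The arithmetic is sound. It is a two-group calculation for one score, one age and one pair of arms at an undivided 0.05.

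**3. Power under different uses of alpha**

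With 492 × 0.80 = 393.6 analysed per arm, the design effect is 1 + (m − 1) × 0.03, and power is Φ(0.25 × √(n_eff/2) − z), with z = 1.960 at alpha 0.05 and 2.241 at alpha 0.025. The 85 clusters come from the Allocation section; equal cluster size is an assumption.

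| Clusters | m | Design effect | n_eff per arm | Power, alpha 0.05 | Power, alpha 0.025 |
|---|---|---|---|---|---|
| 60 (20 per arm) | 19.68 | 1.560 | 252.2 | 80.2% | 71.4% |
| 85 (28.3 per arm) | 13.89 | 1.387 | 283.8 | 84.6% | 76.9% |

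**4. Illustration of the breadth of the primary family**

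Assumptions not found in the article: each score, age and active-versus-Usual-care contrast is tested separately at 5%, and any one significant result counts.

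- CBCL only: 2 scores × 3 ages × 2 contrasts = 12 tests. If independent, 1 − 0.95¹² = 46%.
- Parenting subscales included: 4 × 3 × 2 = 24 tests. If independent, 1 − 0.95²⁴ = 71%.
- The tests are correlated in practice. I simulated three arms under no effect, both contrasts sharing the Usual care arm, with correlations of 0.3-0.7 between scores and 0.5-0.8 between ages. This gave about 27-38% for 12 tests and 40-60% for 24.

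For externalising at age 5 alone, with both contrasts against Usual care at 5%, the figure is about 9%.

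**The case against.** **Multiplicity may be handled elsewhere.** Alpha allocation and testing order are commonly left to an analysis plan, which is not shown. This stands: the absence of a multiplicity procedure in the article is not part of the finding.

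**A reader might infer that the trial may claim success on any of 12 to 24 tests at 5% each.** The article does not say so. The 0.05 in the power section is the design alpha, and the 5% in the Analyses section governs only the test of interaction between caregivers. Separate pairwise tests by age are not specified either; a global three-arm test or a joint model over ages would mean fewer tests. The false-positive rates above therefore remain illustrations.

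**A reader might also infer that Combined versus Targeted has been left out.** That is too strong. The primary comparison is across all three arms, which can include this pair, and the article specifies that contrast for uptake of the Family Check-Up.

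**Co-primary outcomes are legitimate.** This also stands. Nothing obliges the sponsor to demote internalising, the parenting subscales or the earlier ages.

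**The earlier trial is a weak guide.** It tested the universal program alone, with different session timing, so it shows that a parenting-only result is plausible, not that it is expected.

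**Four time points against three ages** need not conflict, since an outcome can be measured at an age that is not in the primary comparison.

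None of this removes the label conflict. An analysis plan could settle it only by overruling part of the article.

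**Conclusion.** The point holds in two parts, both resting on the text alone. First, the article contradicts itself on whether nurturing and harsh discipline are primary, so the verdict on a parenting-only effect is undetermined. Second, the power applies to CBCL externalising at age 5 for in effect one contrast, while the primary analysis is wider and names no deciding test. The sample size arithmetic is correct.

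The consequence for power depends on how alpha is used. At the planned size it is about 80% (60 clusters) to 85% (85 equal clusters) for a single contrast, or for the first in a fixed order. It is about 71-77% per contrast if alpha is split at 0.025. Under Holm that lower range is a floor, because the second contrast is tested at 0.05 once the first has rejected. The false-positive figures depend on assumed correlations and an assumed testing scheme, and show only how much the choice between readings could matter.

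This should be corrected, because following the article as written leaves the primary conclusion open.

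**What to change.** Before outcome data are seen:

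1. Give nurturing and harsh discipline one status, and use it in the hypotheses, the Outcome measures section and the Analyses section.
2. Name the primary score, age and arm contrasts. Primary-carer CBCL externalising at age 5 is the natural choice because it is the powered outcome. If co-primaries are kept, state how the error rate across them is controlled.
3. State which contrast and which alpha the 80% refers to. For two contrasts against Usual care, a fixed order or Holm are both workable, and the power should be restated for the one chosen.

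The cost is wording, and possibly a less favourable stated power. If a single contrast on externalising at age 5 is named, the 393 analysed and 492 recruited per arm stand unchanged.

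### A 5% interaction test decides whether the carers' effects are reported separately or pooled, and declared primary outcomes are not exempted

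*Protocol article*

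**What the plan says.** The first paragraph of Analyses fixes the primary analysis by reporter and without condition: "Primary analyses will compare the mean CBCL externalising and internalising scores reported by the primary caregiver at ages 3, 4 and 5 years". The second paragraph turns to secondary work: "Secondary analyses will compare the CBCL scores reported by the secondary caregiver and, for both caregivers, compare mean parenting subscale scores". It then adds a test and a reporting rule. The test is stated as "Tests of interaction will be used to investigate whether the intervention effects differ between outcomes reported by the primary and secondary caregivers". The rule opens "If there is evidence at the 5% level of significance of differential effects then separate effect sizes will be reported for each caregiver, otherwise", and its alternative reads in full "otherwise a single overall effect size will be reported".

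Two other places bear on this. The hypotheses at the end of the Background, and the Outcome measures section, both name harsh discipline and nurturing parenting as primary outcomes alongside CBCL. Power calculation and study population sizes the trial for one comparison only: a 0.25 SD difference between arms in CBCL externalising score at age 5.

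**The concern.** The rule is a pretest. Its result chooses between two different quantities: an effect for each carer, or an average over carers. Failing to reject equality at 5% does not show that the effects are equal, least of all in a trial not sized for the interaction. If the secondary-carer effect is the smaller one, the pooled figure is pulled below the primary-carer effect that the trial was designed to estimate. An interval computed as if no pretest had been made does not have its nominal coverage.

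The rule reaches declared primary outcomes. For CBCL, the test has to use the primary-carer scores, and nothing says that the primary-carer effect is still reported when the test is not significant. Nurturing and harsh discipline appear in Analyses only in this paragraph, so the rule applies to them on any reading. For parenting and parental mental health, each carer presumably reports on themselves, so an average over carers also answers a different question.

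**Working it through.** **1. The plan's own sample size.** Inputs from Power calculation and study population: 0.25 SD, 80% power, two-sided 0.05, 20 clusters per arm, ICC 0.03, 20% attrition.

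- Without clustering: n = 2(1.96 + 0.84)²/0.25² ≈ 251, stated as 252 per arm.
- Fixed number of clusters: m = n(1 − ICC)/(k − n·ICC) = 252 × 0.97/(20 − 7.56) = 19.65 per cluster, and 20 × 19.65 = 393 per arm.
- Attrition: 393/0.8 = 491.25, so 492.

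All three figures reproduce. The design effect is 1 + 18.65 × 0.03 = 1.56, the effective n is 393/1.56 = 252, and main-effect power is 80.1%.

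**2. Power of the interaction test.** The documents give neither the correlation ρ between the two carers' scores nor the secondary-carer response. Assumed: ρ from 0.3 to 0.7 and response from 50% to 100%. The within-family difference has SD √(2(1 − ρ)), so for n pairs per arm SE = √(2(1 − ρ)) × √(2/n) and power ≈ Φ(d/SE − 1.96). These calculations already use the pairing within family. The clustering of the difference is unknown, so two cases bracket it: ICC 0.03 (design effect 1.56 at full response, 1 + 8.825 × 0.03 = 1.26 at 50%) and none.

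Power to detect 0.25 versus 0.125 SD (d = 0.125):

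| Response | Clustering | ρ = 0.3 | ρ = 0.5 | ρ = 0.7 |
|---|---|---|---|---|
| 100% | ICC 0.03 | 21.9% | 28.9% | 44.1% |
| 100% | none | 31.6% | 41.8% | 61.9% |
| 50% | ICC 0.03 | 15.2% | 19.5% | 29.5% |
| 50% | none | 18.1% | 23.5% | 35.9% |

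Example: ρ = 0.5, n = 252 gives SE = 1 × √(2/252) = 0.0891, 0.125/0.0891 = 1.403, and Φ(−0.557) = 28.9%. A two-degree-of-freedom test over three arms, with the same difference in both active arms and no clustering, gives a similar range of 17.5% to 64.3%. The rule therefore pools in about 38% to 85% of such trials.

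**3. What is reported.** With equal weights the pooled target is (0.25 + 0.125)/2 = 0.1875. If reports are weighted by number and secondary response is 50%, it is (0.25 + 0.5 × 0.125)/1.5 = 0.208. The rule was simulated (400,000 replicates, full response, effective n 252), taking the primary-carer effect when the test is significant and the pooled effect otherwise:

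| True 0.25 v 0.125 | ρ = 0.3 | ρ = 0.5 | ρ = 0.7 |
|---|---|---|---|
| Mean reported effect | 0.217 | 0.221 | 0.229 |
| Coverage of 0.25 | 87.2% | 88.9% | 91.0% |
| Power | 79.4% | 75.7% | 74.5% |

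Always reporting the primary-carer effect gives no bias, 95% coverage and 80.1% power. With no effect in either carer, the type I error of the rule is 5.4% to 6.0%.

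**4. Other true states.**

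- Nil secondary-carer effect (0.25 v 0): interaction power is 66.0% to 99.5% at full response and 46.1% to 89.2% at 50%. When the test misses, the pooled target is 0.125. At full response with design effect 1.56, coverage of 0.25 is 83.2%, 89.3% and 93.9% for ρ = 0.3, 0.5 and 0.7.
- Equal effects (0.25 v 0.25): no bias, coverage about 94% to 95%, and power rises to about 86% to 92%.

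**The case against.** The strongest reply is textual. Primary-carer CBCL is declared primary without condition, and the rule comes later, in a paragraph that opens with secondary analyses. A natural reading is that the primary result stands and the rule only governs how the two-carer comparison is summarised. A reader might infer that the plan intends the pooled figure to replace the primary CBCL result; the document does not say so. It does not exclude it either, and the reply gives no protection to nurturing and harsh discipline, whose only analysis lies in that paragraph.

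A reader might also infer that the interaction test has a wrong standard error, because the plan states "All analyses will allow for correlation between outcome scores of participating families from the same MCH cluster" and names no family-level term. That does not follow. Allowing for cluster correlation does not exclude other terms, Analyses specifies random-effects regression without listing the effects, and a condensed article commonly leaves that to the full plan. No claim about the size of the test is made here.

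Finally, the loss depends on assumed inputs. A smaller secondary-carer effect is plausible but not shown: the Family Check-Up is described for one or more primary caregivers and the groups for parents, so attendance is not limited to one carer. With equal effects, pooling helps. The loss of power in the half-size case is modest, about 1 to 6 percentage points. All of this stands, and it limits the size of the point without making a non-significant test into evidence of equality.

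**Conclusion.** The concern holds in a limited form. As written, the rule lets the data choose the reported quantity through a test that the trial was not sized for, and it exempts no declared primary outcome. For primary-carer CBCL this is an ambiguity to close; for nurturing and harsh discipline the rule applies directly.

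The size rests on assumptions outside the documents. For a secondary-carer effect half the primary-carer effect, the test detects the difference in about 15% to 62% of trials, and pooled results aim at about 0.19 SD (equal weights) in place of 0.25. At full response and design effect 1.56, coverage is about 87% to 91%. If the secondary-carer effect is nil and response is good, the difference is usually detected and the average bias is smaller, although coverage still falls to 83.2% at ρ = 0.3. If the effects are equal there is no bias. The plan should be changed, but nothing here shows that the declared primary analysis is invalid.

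**What to change.** Replace the pretest rule with a fixed one. For each outcome collected from both carers, including CBCL, nurturing and harsh discipline, always report the primary-carer effect as the primary result (or as the main result where the outcome is secondary) with the secondary-carer effect alongside, whatever the interaction test shows. Report the arm-by-caregiver interaction with its confidence interval, and any pooled estimate, as supplementary. State that any model using both carers' reports accounts for their pairing within family as well as for MCH cluster; if the full plan already says so, nothing changes there.

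The cost is plan wording. No further data are needed, and the carer-specific effects must be estimated for the interaction test in any case. What is given up is the gain in power from pooling as the headline result when effects are equal; the supplementary pooled estimate still shows it.
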